### 3.6. Statistical Analysis

Baseline clinical and echocardiographic characteristics of each group will be examined and compared using the chi-square test for categorical variables and the two-sided Student’s *t*-test or the analysis of variance (ANOVA) test for continuous variables depending on the number of groups. Categorical variables will be represented by frequencies and percentages (%) and continuous variables will be summarized by mean ± standard deviation. Comparison of changes in echocardiographic indexes between admission and discharge will be performed using the paired *t*-test or Wilcoxon signed rank test according to the normality of distribution.

Univariate and multivariate logistic regression analysis and Cox regression analysis will be performed to identify independent predictors of outcome at follow-up. Only covariates that are significantly associated with the endpoint at univariate analysis will be included in multivariate models. The sensitivity and specificity of resulting echocardiographic parameters for the prediction of early mortality, late mortality, and rehospitalization will be evaluated with receiver operating characteristic curves. To assess the potential additive prognostic value of novel imaging biomarkers over baseline models, the additional increase of the chi-square value will be assessed using the likelihood ratio test. A time-to-event analysis will be performed according to the Kaplan–Meier method to assess whether groups of patients with specific echocardiographic patterns are associated with better or worse clinical prognosis. Event rates will be compared by the long-rank test. A two-tailed *p* value of 0.05 will be considered the significance threshold for all statistical tests. All outcomes will be reported with 95% confidence intervals. Data management and statistical analyses will be conducted using SPSS software, version 26 (IBM SPSS Statistics) and R version 3.4.4 (R Foundation for Statistical Computing, Vienna, Austria).

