Accordingly, using—among others—novel echocardiographic imaging biomarkers, this observational study aims to investigate (i) the intrahospital echocardiographic variations of diverse acute HF phenotypes as a response to acute treatment, (ii) the improvement or deterioration of all chambers’ systolic function parameters and echocardiographic markers of congestion during the acute HF episode, (iii) the association of admission or discharge echocardiographic parameters with early mortality, late mortality, and HF rehospitalization, and (iv) whether suboptimal echocardiographic improvement at discharge in response to acute HF treatment is associated with poor prognosis.

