## 2. Methods and Materials

### Study Design and Population

The “Beyond Myo-HF Study” (ClinicalTrials.gov Identifier: NCT05573997) is an investigator-initiated, prospective, non-interventional cohort trial involving patients with acute HF. A total of 300 consecutive patients acutely admitted to the Department of Cardiology of AHEPA University General Hospital, Thessaloniki, Greece with symptoms and/or signs of HF satisfying the inclusion criteria are enrolled in the present study. Eligibility criteria are described in Table 1.

Demographic characteristics and baseline medical history including a history of previous hospitalization for acute HF, primary etiology, and clinical presentation of hospitalization are recorded for all participants. Pharmacological and non-pharmacological therapeutic maneuvers during the acute phase of hospitalization, as well as medical therapy upon admission and discharge, are collected. A comprehensive transthoracic echocardiographic assessment (TTE) is performed at two different time-points during hospitalization. The first TTE is performed within 24 h from admission, and the second with 24 h pre-discharge, to capture the trajectory and net variations of all echocardiographic indices of interest. A cardiac computed tomography or cardiac magnetic resonance study will be routinely performed as required to investigate the primary HF cause for undiagnosed patients. In addition, patients’ laboratory results including complete blood count, biochemical control, inflammatory markers, coagulation mechanism control, hormonal control, N-terminal pro-B-type natriuretic peptide, and high sensitivity troponin T levels are collected upon admission and prior to discharge (Figure 1).

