In the current study, the response to acute HF therapy will be assessed, among others, by computation of non-invasive LV myocardial work parameters. Such novel indices are estimated via dedicated software by integrating speckle tracking LV GLS, blood pressure as an afterload estimate, and cardiac event timing to formulate a pressure–strain loop of the LV [7]. Accounting for dyssynchrony and afterload, LV global myocardial work has shown to provide incremental prognostic information over and above LV GLS and LVEF regarding all-cause mortality or HF hospitalization between subjects with heart failure with reduced ejection fraction [21]. Additionally, Hedwig et al. displayed that LV GWI and LV GCW could independently predict events among a group of advanced HF patients [22]. Only one study has assessed dynamic in-hospital changes of myocardial work indices for acute HF patients and observed improvement of GCW and GWI only for heart failure with reduced ejection fraction but not heart failure with preserved ejection fraction patients [23]. The prognostic implications of those intrahospital changes were not investigated in the aforementioned work [23].

The RV is a thin-walled cardiac chamber with low ventricular elastance, whose contractile properties are more susceptible to its loading environment, preload, and afterload, compared with the LV [24]. Those characteristics render the RV more vulnerable to acute changes in hemodynamic conditions and thus suited for serial echocardiographic assessment to identify response to intensive therapy and recovery after an acute HF episode [6]. Reducing peripheral congestion or pulmonary pressures would have a strong impact on RV size and function. RVMW, combining information on contractile function by stain analysis and on afterload assessed by PASP, is an echocardiographic parameter that could reflect alterations in response to acute treatment. This study aims to expand the current literature by investigating the intrahospital changes and prognostic significance of RV myocardial work in acute HF.

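### The only test named for in-hospital change is a paired test, so the stated analysis cannot show whether change differs between the heart failure phenotypes of aim (i)

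*Protocol article*

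**What the plan says.** The Introduction lists four aims. Aim (i) is to investigate "the intrahospital echocardiographic variations of diverse acute HF phenotypes as a response to acute treatment". Aim (ii), listed separately, is "the improvement or deterioration of all chambers’ systolic function parameters and echocardiographic markers of congestion during the acute HF episode".

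The Methods (Study Design and Population) form the groups: three LVEF classes from the admission echocardiogram (40% or less, 41–49%, 50% or more), and new-onset versus chronic heart failure by previous hospitalization. The sample is "A total of 300 consecutive patients acutely admitted to the Department of Cardiology". Class sizes are not given.

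Section 3.6 then assigns the tests. For groups: "Baseline clinical and echocardiographic characteristics of each group will be examined and compared using the chi-square test for categorical variables", with the t-test or ANOVA for continuous variables. For change: "Comparison of changes in echocardiographic indexes between admission and discharge will be performed using the paired *t*-test or Wilcoxon signed rank test", chosen by normality. The regression, ROC and Kaplan–Meier analyses that follow concern outcome. For every test a two-tailed "value of 0.05 will be considered the significance threshold for all statistical tests".

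**The concern.** No test in section 3.6 has the null hypothesis that change is equal across phenotypes. There are two ways to run the paired tests. If they are pooled over all patients, aim (i) receives no analysis by phenotype. If they are run in each class, the only contrast on offer is that one class reached significance and another did not, which is not a test of a difference.

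That kind of statement is familiar in this field. Section 4 summarises the one earlier study of in-hospital change in myocardial work as having "observed improvement of GCW and GWI only for heart failure with reduced ejection fraction but not heart failure with preserved ejection fraction patients". A reader of the new study would naturally look for the same kind of statement.

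Two errors are possible. A phenotype-specific response could be reported when all classes change equally, or a real difference could go unnoticed because every class improves significantly.

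**Working it through.** The article gives no effect size, SD, power or class sizes, so there is no stated figure to reproduce. The check asks how often separate paired tests mislead.

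**Inputs from the article.** N = 300; two-sided alpha 0.05; three LVEF classes.

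**Assumptions.** Change scores are normal with equal SD. True change d is in SD units of the change score. Class sizes (reduced/mildly reduced/preserved) are 100/100/100, 150/50/100 or 180/45/75.

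**1. Power in one class.** The paired t-test has n − 1 degrees of freedom and noncentrality d√n. At d = 0.2:
- n = 150: 0.2 × √150 = 2.45, power 0.682
- n = 100: 0.2 × √100 = 2.00, power 0.508
- n = 50: 0.2 × √50 = 1.41, power 0.284

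**2. Disagreement when all classes share the same true change.** P(at least one significant and at least one not) = 1 − Πpᵢ − Π(1 − pᵢ).

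For 150/50/100 at d = 0.2: 1 − (0.682 × 0.284 × 0.508) − (0.318 × 0.716 × 0.492) = 1 − 0.098 − 0.112 = 0.790.

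With no change in any class: 1 − 0.05³ − 0.95³ = 0.143. This is the reference value, not 5%.

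| True change (SD) | 100/100/100 | 150/50/100 | 180/45/75 |
|---|---|---|---|
| 0 | 14.3% | 14.3% | 14.3% |
| 0.1 | 41.9% | 42.3% | 42.7% |
| 0.2 | 75.0% | 79.0% | 81.5% |
| 0.3 | 39.5% | 55.6% | 63.9% |
| 0.4 | 6.7% | 22.8% | 30.7% |
| 0.5 | 0.4% | 6.7% | 10.3% |

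Simulation (20,000 runs) at 0.2 and 0.3 SD agreed with these values. In the same runs a one-way ANOVA on the change scores rejected in 4.7–5.5%.

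**3. A real difference missed.** Let two classes truly change by 0.4 and 0.8 SD. Both paired tests are significant with probability 0.977 (100 and 100 patients), 0.998 (150 and 100) or 1.000 (180 and 75), so the p-values show no contrast. A direct test of the 0.4 SD difference has power 0.81, 0.87 and 0.83.

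**4. A limit of the direct test.** Step 2 treats class as independent of measurement error on the admission scan. For LVEF this fails, because that scan both sets the class and supplies the baseline of the change score. Simulations gave every patient the same true LVEF change, with an assumed true SD of 14 points and N = 300. The one-way test on LVEF change rejected in about 50% of trials at a scan error SD of 3 points, rising to about 92% at 5 points. For another index whose admission error correlates 0.3–0.5 with LVEF error, it rejected in about 9–35%. With independent error it stayed near 5%.

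**The case against.** The strongest reply is that this is an omission in a condensed article, and that an SAP not shown may specify the comparison. What section 3.6 does state is sound for aim (ii), since a paired test is the right tool for improvement or deterioration over the episode. Aim (i) can also be read as describing each phenotype, as it states no hypothesis that they differ.

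Much of this stands, and it limits the point. A reader might infer any of the following, and the article supports none of them:

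- **That the study will report false phenotype differences.** Section 3.6 does not say that paired tests are run by class or that their p-values are compared.
- **That unequal class sizes are the cause.** At 0.2 SD, equal classes already disagree in 75%, against 79–82% for the unequal splits. Intermediate power drives most of it, although imbalance adds more at 0.3–0.4 SD.
- **That the risk applies to every index.** It is nearly gone by 0.5 SD. Section 4 cites a 176-patient study in which several congestion indices improved across all LVEF groups, so agreement is plausible for those.
- **That the earlier myocardial-work study drew its contrast from separate p-values.** The article does not say how that result was tested.

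The reply does not remove the core. Section 3.6 is not merely silent: it selects a test for change and places the between-group tests at baseline. Under either reading of the paired tests, the stated analysis cannot support a phenotype contrast.

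**Conclusion.** The point holds in a limited form. As stated, the analysis can describe change but cannot show whether it differs between LVEF classes or between new-onset and chronic heart failure. If class-wise paired p-values are read against each other, an equal true change of 0.1–0.3 SD makes the classes disagree in about 40–80% of trials, against about 14% with no change. The figure is about 10% or fewer at 0.5 SD. The opposite error, a real difference hidden because all classes improve, is also possible.

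These figures rest on assumed class sizes, normal change scores with equal SD, and a by-class reading that the article does not state. The matter is worth correcting because the remedy uses data already collected, but the simple remedy is unsafe for LVEF itself and needs care for indices that share its measurement error.

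**What to change.** In section 3.6:

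1. Keep the paired tests as a description of change.
2. State that any claim that in-hospital change differs between phenotypes rests on a direct between-group comparison (a group-by-time interaction or a between-group test of the change score), reported as the difference in change with its 95% CI. Differences will not be inferred from separate paired p-values.
3. State that change in LVEF will not be compared between LVEF classes in this way, because class is defined on the admission scan. Interpret LVEF-class contrasts for indices whose error is correlated with LVEF, such as LV GLS, with a stated regression-to-the-mean caution. Adjusting for the admission value would not fully settle LVEF itself.

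The cost is a few sentences and one extra model per index, with no new data. The small downside is that fewer phenotype differences will be declared.

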## Abstract

Background. Despite ongoing treatment advancements in chronic heart failure (HF), mortality and readmission rates remain high for patients hospitalized for decompensated acute HF. These patients represent a distinct HF group, which requires emergent echocardiographic evaluation in an attempt to provide optimal and individualized acute care. The role of serial advanced echocardiographic assessment in acute HF for risk stratification and treatment guidance has not been thoroughly explored. Methods. The “Beyond Myo-HF Study” is a prospective, non-interventional cohort trial designed to enroll acutely admitted patients with symptoms and/or signs of HF. The aim of this study is to investigate whether intrahospital changes of conventional and novel echocardiographic indices of myocardial function and congestion-related markers can predict early mortality, late mortality, and HF rehospitalization. As per the protocol, all patients undergo a pair of state-of-the-art echocardiographic assessments, with a rigorous protocol including speckle tracking analysis of all cardiac chambers and myocardial work analysis for the left and right ventricle, upon admission and pre-discharge. Their laboratory profile is captured at those two time-points, and their therapeutic management is recorded. Patients will be followed-up for a median period of 12 months after enrollment. Conclusions. The “Beyond Myo-HF” study is an ongoing, prospective trial aspiring to provide deep insight into the pathophysiology of acute HF, to enlighten the reverse cardiac functional and anatomical remodeling during hospitalization, and to recognize echocardiographic patterns capable of predicting adverse outcomes during and post decompensation of acute HF.

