Before each TTE study, heart rate and brachial blood pressure using a conventional sphygmomanometer are recorded. Additionally, height and weight of each participant are recorded and utilized to determine body mass index and body surface area in accordance with the Dubois formula [9]. Informed written consent is obtained from all participants prior to study enrollment. All patients undergo standard of care acute HF management, as dictated by their clinical presentation, the practice of the hospital, and most updated guidelines [10]. The investigation conforms with the principles outlined in the Declaration of Helsinki (2013 Amendment), and the study protocol was approved by the Ethics Committee of the School of Medicine of Aristotle University of Thessaloniki (Approval number: 19/2022, Date of approval: 10 November 2022).

In accordance with the guideline-recommended HF definitions [10], HF patients are classified on the basis of their left ventricular ejection fraction (LVEF), as this is calculated from the admission TTE study. Those are patients with (i) heart failure with reduced ejection fraction (LVEF ≤ 40%), (ii) heart failure with mildly reduced ejection fraction (LVEF = 41–49%), and (iii) heart failure with preserved ejection fraction (LVEF ≥ 50%). In addition, patient are classified as new-onset or chronic HF, on the basis of a previously documented HF hospitalization. The trend of their echocardiographic profile during hospitalization is recorded to identify predictors of early and late mortality, and HF rehospitalization at follow-up. Follow-up data are collected regularly by independent physicians via in-person or telephonic interviews. All deaths are ascertained by searching in the Greek web-based national health insurance system. Other clinical outcomes, apart from death, are identified either through hospital reports or by telephone contact.

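### For late mortality and HF rehospitalization, logistic regression and ROC curves are planned over a follow-up fixed only by its median, so unequal observation time is not accounted for

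*Protocol article*

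**What the plan says.** All references are to the protocol article.

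- **Follow-up (Abstract):** "Patients will be followed-up for a median period of 12 months after enrollment". The article gives no minimum, maximum, common closing date or fixed horizon.
- **Endpoints (Study Design and Population):** the echocardiographic trend is recorded "to identify predictors of early and late mortality, and HF rehospitalization at follow-up". Neither early nor late is given a time window.
- **Regression (section 3.6):** "Univariate and multivariate logistic regression analysis and Cox regression analysis will be performed to identify independent predictors of outcome at follow-up". The two models are not assigned to particular endpoints.
- **Discrimination (section 3.6):** the sensitivity and specificity of the retained echocardiographic measures "for the prediction of early mortality, late mortality, and rehospitalization will be evaluated with receiver operating characteristic curves". No horizon and no censoring-adjusted version is named.
- **Methods that handle censoring (section 3.6):** besides Cox, "A time-to-event analysis will be performed according to the Kaplan–Meier method", with a log-rank comparison.
- **Ascertainment (Study Design and Population):** "All deaths are ascertained by searching in the Greek web-based national health insurance system". For the rest: "Other clinical outcomes, apart from death, are identified either through hospital reports or by telephone contact".

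**The concern.** Logistic regression and a conventional ROC curve need a yes/no status for each patient over the same period. That is unproblematic for a short early window in which everyone's status is known. It is a problem for late mortality and rehospitalization if some patients are watched for, say, 6 months and others for 18.

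The analyst must then do something with a patient who is event-free when observation stops early. Coding that patient as a non-event turns some true events into non-events. Dropping the patient removes mainly non-events and raises the apparent event proportion. Counting any event during whatever follow-up exists lets patients with long follow-up collect more events.

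At stake are the sensitivity, specificity and AUC of the novel echocardiographic markers for the late outcomes, and any odds ratio reported for them. Section 3.6 takes these sensitivities and specificities from the ROC curves, so the Cox and Kaplan–Meier analyses do not replace them.

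**Working it through.** The article gives no power, event count or late event rate to reproduce, so this check is an illustration.

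**Input from the article:** median follow-up of 12 months.

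**Assumed inputs:**
- follow-up C uniform on 6–18, 3–21 or 0–24 months (each with median 12), or exactly 12 months;
- a standard normal marker x with hazard ratio 1.6 per SD;
- 12-month event risk of 15%, 30% or 50%.

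**Method:** the event time T is exponential with hazard λ × 1.6^x. λ is set so that the mean of 1 − exp(−12 λ 1.6^x) equals the assumed risk. There are 400,000 patients per scenario. True status is 1 if T ≤ 12. Event-free coding gives 1 only if T ≤ min(C, 12). Each status is regressed on x by logistic regression, and its AUC is computed.

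**Hand check on missed events.** If events fall evenly over 12 months, the share falling after observation stops is (1/12) × ∫ P(C < t) dt over 0 to 12:
- 6–18 months: (6² / (2 × 12)) / 12 = 0.125
- 3–21 months: (9² / (2 × 18)) / 12 = 0.1875
- 0–24 months: (12² / (2 × 24)) / 12 = 0.25

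The simulated shares at 15% risk are 0.115, 0.174 and 0.243. They are slightly lower because events occur somewhat earlier than evenly.

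**Follow-up independent of the marker:**

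| 12-month risk | Follow-up (months) | Status unknown at 12 months | True events missed | OR, true → event-free coding | AUC, true → event-free coding |
|---|---|---|---|---|---|
| 15% | 6–18 | 44.2% | 11.5% | 1.68 → 1.67 | 0.640 → 0.639 |
| 15% | 0–24 | 46.2% | 24.3% | 1.68 → 1.66 | 0.641 → 0.637 |
| 30% | 6–18 | 38.2% | 10.9% | 1.77 → 1.74 | 0.651 → 0.648 |
| 30% | 3–21 | 39.9% | 16.6% | 1.78 → 1.73 | 0.652 → 0.646 |
| 30% | 0–24 | 42.0% | 22.9% | 1.77 → 1.69 | 0.651 → 0.641 |
| 50% | 6–18 | 29.9% | 9.3% | 1.94 → 1.88 | 0.672 → 0.665 |
| 50% | 0–24 | 35.8% | 21.6% | 1.96 → 1.77 | 0.674 → 0.651 |

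If everyone is followed for exactly 12 months, nothing is missed and both codings agree.

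**Dropping instead of coding event-free (30% risk).** The event proportion among patients with known status is 0.268 / (1 − 0.382) = 0.43 for 6–18 months and 0.231 / (1 − 0.420) = 0.40 for 0–24 months. The true value is 0.30.

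**Follow-up correlated with the marker (30% risk):**

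| Follow-up (months) | r | OR, true → event-free coding | AUC, true → event-free coding |
|---|---|---|---|
| 6–18 | −0.3 | 1.76 → 1.63 | 0.651 → 0.632 |
| 6–18 | +0.3 | 1.77 → 1.86 | 0.651 → 0.663 |
| 0–24 | −0.3 | 1.76 → 1.43 | 0.650 → 0.599 |
| 0–24 | +0.3 | 1.77 → 1.94 | 0.650 → 0.673 |

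**Events concentrated early.** Suppose 15% die by month 2 and 25% or 40% by month 12. With follow-up of 6–18 months, 14.2% or 13.4% of the deaths in months 2–12 are missed. No earlier death is missed, so the share of all 12-month deaths is 0.142 × 10/25 = 5.7% or 0.134 × 25/40 = 8.4%.

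**Early window.** With a horizon of 1 or 2 months, the share of patients observed for less than the horizon is 0 for 6–18 and 3–21 months. For 0–24 months it is 1/24 = 4% or 2/24 = 8%.

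**The case against.** The strongest reply is that this is a condensed article on an exploratory cohort, and that coding rules and horizons may stand in an analysis plan that is not shown. Cox, Kaplan–Meier and log-rank, which handle censoring, are already planned. Deaths are sought in a national system, so vital status at a fixed date may be easy to obtain. Logistic regression may be meant for early mortality and Cox for the late outcomes. Where follow-up is unrelated to the marker, the OR and AUC barely move, and the article does not suggest that enrolment date tracks echocardiographic findings.

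Much of this stands, and it rules out several stronger readings that a reader might infer:

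- **Censored patients are counted as event-free.** The article does not describe the coding, so this is one possibility and not a stated plan.
- **Half the patients are observed for less than 12 months.** A median does not give the spread. It is also 12 if everyone is followed for exactly 12 months, and short follow-up caused by death is an event and not censoring.
- **Logistic and Cox are both run on the same endpoint, giving two chances of a finding.** The text names both for a generic outcome and assigns neither.
- **All outcomes are affected.** Early mortality is hardly touched.

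What does not fall is the ROC analysis. Section 3.6 names late mortality and rehospitalization for it, and no horizon is set anywhere. Cox and Kaplan–Meier do not supply the planned sensitivities and specificities. The national search limits loss to follow-up for death, but without a common horizon it does not equalise observation time. It does not cover rehospitalization, which relies on hospital reports or telephone contact.

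**Conclusion.** The point holds for late mortality and HF rehospitalization, at moderate severity. The article names binary methods for outcomes whose observation time it leaves open, and better methods are readily available.

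The size depends on assumptions about the spread of follow-up, the event risk and the marker effect, none of which the article gives. Under the assumed spreads with independent follow-up, 30–46% of patients have unknown 12-month status and 9–24% of true events would be missed by event-free coding. The OR and AUC are still only mildly attenuated. The largest change is OR 1.96 to 1.77 and AUC 0.674 to 0.651, at 50% risk and 0–24 months. A material distortion, in either direction, needs follow-up length to be correlated with the marker, which is an assumption here. It would be too strong to conclude that the late results will be seriously biased. What can be said is that the named methods give no protection if observation time differs.

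**What to change.** 1. Make Cox regression the inferential model for late mortality and HF rehospitalization.
2. Restrict logistic regression and standard ROC curves to a fixed early window, stated in days, in which every patient's status is known.
3. For the late outcomes, use time-dependent ROC/AUC at stated horizons (for example 12 months) with inverse-probability-of-censoring weights. For rehospitalization, state how death before readmission is treated.
4. Alternatively, for death, read vital status at a fixed day 365 for every patient from the national system. A conventional 12-month ROC curve is then valid for mortality.
5. State the minimum follow-up or closing date in place of a median alone.

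The cost is revised wording, slightly more analysis work with standard R packages and, at most, a data lock delayed until the last patient reaches 12 months.

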## 1. Introduction

Hospitalized patients with acute heart failure (HF) represent an understudied, distinct group of patients which has mainly been characterized through registries [1]. These patients largely differ from stable outpatients with chronic HF in terms of clinical course, and continue to suffer very poor prognosis; they have an estimated mortality and readmission rate of 15% and 30%, respectively, between the first and second month post discharge [2]. In this regard, it is of paramount importance to identify vulnerable subjects in order to intensify their follow-up and outpatient care. Suboptimal echocardiographic improvement in response to acute HF treatment may represent a red flag but current literature is scarce.

In acute decompensated HF, intensive therapy aims to lessen intracardiac pressure and central venous congestion [3], which is expressed as an improvement of the circulatory volume-dependent echocardiographic parameters, mainly evidenced through reverse remodeling of the thin-walled right ventricle (RV). It has been suggested that improvement of RV function surrogates such as tricuspid annular plane systolic excursion (TAPSE) and right ventricular–pulmonary artery (RV–PA) coupling is of prognostic relevance [4]. However, TAPSE has obvious limitations as it poorly reflects overall contractility of the RV [5], and it has been surpassed by speckle tracking echocardiography with longitudinal strain, which is sensitive in detecting dynamic improvement in RV mechanics [6].

Longitudinal strain does not integrate ventricular dyssynchrony into its quantitative output and does not account for the afterload, which is subject to considerable alterations with the intensive acute HF medical therapy particularly for the RV. Myocardial work is a non-invasively derived index of myocardial function that accounts both for ventricular dyssynchrony and afterload [7]. Although originally dedicated for the left ventricle, this method has recently been evaluated for the RV and has shown significant correlation with invasively measured RV stoke volume [8]. Nonetheless, its prognostic implications in the acute HF setting have not been comprehensively investigated so far.

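### Admitting only univariately significant covariates to the multivariable models lets chance decide the adjustment set, so real confounders will often be left out and the intervals ignore the selection

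*Protocol article*

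**What the plan says.** Section 3.6 (Statistical Analysis) plans univariate and multivariate logistic and Cox regression that "will be performed to identify independent predictors of outcome at follow-up". The entry rule is: "Only covariates that are significantly associated with the endpoint at univariate analysis will be included in multivariate models". The cut-off follows from the same section, where a two-tailed p "value of 0.05 will be considered the significance threshold for all statistical tests".

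Three endpoints are in view; the ROC analysis, for example, is planned "for the prediction of early mortality, late mortality, and rehospitalization will be evaluated". The cohort is "A total of 300 consecutive patients acutely admitted", and the Abstract states: "Patients will be followed-up for a median period of 12 months after enrollment". Each patient is scanned at admission and before discharge "to capture the trajectory and net variations of all echocardiographic indices of interest". Admission values, discharge values and in-hospital changes are therefore all candidate predictors, as the Abstract and the aims at the end of the Introduction confirm.

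Section 3.6 also plans a likelihood-ratio test of novel markers over baseline models. It does not name the covariates of those models, and nothing exempts them from the entry rule.

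**The concern.** An independent predictor is one that holds after adjustment. Here the adjustment set is whatever reaches p<0.05 on its own in this sample. A clinical variable that truly confounds an echocardiographic index is excluded if its crude association falls short, and no covariate is kept on clinical grounds. The set can also differ by chance from one endpoint to the next. Indices that do pass are those whose estimates happened to be large, and the promised 95% confidence intervals take no account of that.

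This is an observational cohort whose Limitations section concedes that treatment is individualised and may change daily, so confounding matters. The rule is written into the article; it is not a detail left open for a fuller plan.

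**Working it through.** The plan gives no event number, effect size or power, so there is no figure of its own to reproduce. The check is what the entry rule does at plausible event counts.

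**Inputs**
- n = 300; two-sided 0.05, critical value 1.96 (from the article).
- Event rates of 15% and 30%. The Introduction says of such patients that "they have an estimated mortality and readmission rate of 15% and 30%, respectively, between the first and second month post discharge". These are background rates, used here as an assumption: 300 × 0.15 = 45 events and 300 × 0.30 = 90. Twelve-month counts may be higher.
- Effect sizes and correlations below are assumed.

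**1. A binary covariate passing the screen (Schoenfeld formula)**

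P(pass) = Φ(√(D·q(1−q))·ln HR − 1.96), with D events and prevalence q = 0.30.
- D = 45: √9.45 = 3.074. HR 1.5 gives 3.074 × 0.405 − 1.96 = −0.71, so 24%. HR 2.0 gives 57%.
- D = 90: √18.9 = 4.347. HR 1.5 gives 42%; HR 2.0 gives 85%.

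A covariate with a true hazard ratio of 1.5 is thus dropped about 76% of the time at 45 events and 58% at 90.

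**2. Marker and confounder masking each other**

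Both have OR 1.5 per SD (log 0.4055) and correlation −0.5. The crude log OR of either is about 0.4055 × (1 − 0.5) = 0.2027. The SE is about 1/√(n·p(1−p)): 1/√38.25 = 0.162 at 15% and 1/√63 = 0.126 at 30%.
- Crude z = 0.2027/0.162 = 1.25 and 0.2027/0.126 = 1.61. The pass probability is about 24% and 36%, so the confounder is dropped in about 76% and 64%. The marker faces the same screen.
- In a prespecified joint model the SE is divided by √0.75, giving 0.187 and 0.145. Then z = 2.17 and 2.79, and power is about 58% and 80%.

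Simulation agrees:

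| | 45 events | 90 events |
|---|---|---|
| True confounder dropped | 77% | 68% |
| True marker found, screening rule | 24% | 35% |
| True marker found, prespecified model | 57% | 77% |

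A second, separate run gave 63–77% dropped, and 26–32% found against 62–77%.

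**3. Inflation among estimates that pass**

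True OR 1.25 (log 0.223). Treating the estimate as normal and conditioning on z > 1.96:
- 45 events: P(pass) = 28%; mean log OR = 0.223 + 0.162 × 0.337/0.281 = 0.417, OR 1.52.
- 90 events: P(pass) = 43%; mean log OR = 0.223 + 0.126 × 0.392/0.425 = 0.339, OR 1.40.

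Simulation gave 1.53 at 45 events and 1.41–1.42 at 90. These are univariate odds ratios conditional on passing, not adjusted hazard ratios.

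**4. Linked candidates**
- Change = discharge − admission. An intercept with all three forms has rank 3 of 4.
- Section 3.5 sets PADP = 1.5 × [PAMP − PASP/3] = 1.5·PAMP − 0.5·PASP. An intercept with all three pressures also has rank 3 of 4.
- Work efficiency is a ratio of constructive work to constructive plus wasted work, so it is not an exact linear combination. Under assumed distributions the variance inflation factors for GWI, GCW, GWW and GWE were about 60, 60, 7 and 6.

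**5. Room in the model**

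At 10 events per term (a rule of thumb), 45 events support about 4 terms and 90 support 9. Sections 3.2 to 3.5 name at least 20 indices: 4 strains, 8 work indices, TAPSE, fractional area change, S', LVEF, PASP, right atrial pressure, and mitral and tricuspid regurgitation grade. Three forms of each give 60 candidates, of which 60 × 0.05 = 3.0 pass by chance per endpoint if none is predictive.

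**The case against.** The best defence has four parts.

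*Singularity is not written into the plan.* A reader might infer that the models cannot be fitted. The rule states a necessary condition for entry, the article speaks of models in the plural, and it nowhere says that all forms of one index go into one model. Exact collinearity arises only if every member of a linked set passes and is entered together; software may then drop one, leaving the retained index arbitrary. This stands, and the point is conditional.

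*Bias has no fixed direction.* A reader might infer that adjusted hazard ratios are pushed away from the null. The documents do not support that. Omitted confounding can act either way, and the worked example in step 2 hides a true marker. With a single null marker and positive confounding, simulation put false declarations at 2.6–4.1% under screening against 4.1–5.1% with a prespecified model. This stands too.

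*Chance findings come from the number of candidates.* The 3.0 expected false entries reflect testing 60 terms. In an all-null simulation (15% events), adding indices one at a time to a forced base model also gave 3.0 false predictors, with at least one in 88% of runs. Screening followed by a joint model left 0.7, with at least one in 51%. One-at-a-time testing is therefore no cure without multiplicity control. This stands and shapes the fix.

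*A base model is already foreseen.* The likelihood-ratio test needs one, and its covariates may properly sit in a fuller plan. But as written the entry rule governs the multivariate models without exception, so this does not remove the problem.

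**Conclusion.** The concern holds in limited form. The article fixes an entry rule that excludes confounders on their sample p-value, makes the adjustment set unstable across endpoints, selects inflated estimates and reports intervals that ignore the selection.

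At an assumed 45 to 90 events, a true confounder in the masking scenario is lost in roughly two-thirds to three-quarters of runs, and the chance of finding a true marker falls to about half or less of that under a prespecified model. These sizes rest on assumed effects, correlations and event rates; masking is an unfavourable case, and more events would soften the result. Collinearity is a conditional risk.

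This should be fixed. It does not invalidate the study: two of the four aims are descriptive, and the authors themselves ask for confirmation in other centres.

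**What to change.** - Delete the univariate-entry sentence.
- Prespecify a small clinical base model from admission data already collected (for example age, a renal marker and log NT-proBNP) and force it in whatever the p-values. Size it to the expected events with room for the index: at 10 events per term, about 3 base terms plus one index at 45 events, and up to 8 plus one at 90.
- Use this model as the baseline model for the planned likelihood-ratio test.
- Add one form of one echocardiographic index at a time. Do not enter admission, discharge and change of the same index together, nor PASP, PAMP and PADP.
- Name a short list of primary indices, or control the false discovery rate across all indices and forms tested.
- If indices must be modelled jointly, use penalised regression with bootstrap validation.

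The cost is analysis wording: no new patients or measurements. Some adjusted effects will look less striking and fewer indices will be declared significant. As the study is ongoing, the change should be made before outcomes are analysed.
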